### Exclusion criteria

People will be excluded if they have a confirmed brain stem or cerebellar stroke or are unable to understand and speak basic-level English. Involvement in ACTIV requires frequent communication with a physiotherapist, in person, by telephone and by text message (SMS message), so using an interpreter is considered impractical.

### Randomisation

Randomisation will occur after the baseline assessment and participants will be assigned to one of two groups, ACTIV or usual care control. Randomisation will be stratified by centre (four locations) with recruitment targets of 32 participants from each of the North Island centres and 16 from each of the South Island centres, commensurate with the number of stroke admissions expected in each location. Stratified block randomisation will be used according to geographic centre and baseline mobility. Baseline mobility will be decided by the FAC: either ‘less mobile’ if they have a level of five or below or ‘more mobile’ if they have a level of six. Given the small numbers, random block sizes will be used according to a plan that ensures, according to simulations, a probability smaller than 0.1% that balance will be broken across strata by four participants or more. The randomisation software will be coded and tested by the study statistician, then handed over to a third independent party for random number generator seeding, execution of allocation, and day-to-day management of the randomisation. The recruiters, assessors and personnel involved in data management and analysis will be blinded to treatment assignment.

### Intervention - ACTIV

The Augmented Community Telerehabilitation Intervention (ACTIV) is a 6-month standardised programme delivered in the participant’s home, focusing on two functional categories: ‘staying upright’ and ‘using your arm’. Within each functional category there are standard exercises addressing key components of the defined function. For each component there are parameters to select and modify, allowing the programme to be individualised. The parameters that can be changed include the support received during an exercise, the number of exercises prescribed and the environment in which the exercise will take place. ACTIV will be delivered by a physiotherapist who has completed a training package that provides a) information on the rationale of ACTIV, b) a menu of exercises with guidelines for treatment selection, c) information on goal setting and d) information to facilitate patients in the transition to increased independence. Patient-centred goals will be set at the first home visit (assessment visit) and the physiotherapist will then select exercises and activities aimed at incremental attainment of these goals. The physiotherapists will have telephone and internet access to a consultant physiotherapist with expertise in this programme and in stroke rehabilitation, with who they can discuss any concerns/questions regarding provision of the programme.

ACTIV consists of four home visits (weeks 1, 2, 12 and 25), five telephone calls (weeks 1, 4, 8, 16 and 20) and text messaging (twice weekly for the first 10 weeks and once weekly for the following 16 weeks). Some people with stroke re-access services following discharge from formal therapy. No effort will be made to prevent the intervention group receiving additional care either publicly or privately.

### Initial assessment and exercise prescription

The physiotherapist will work with the participant to identify a goal using the phrase ‘What do you want to do most?’ Once this activity has been selected, the therapist will then explore the participant’s perception of why they are unable to complete this activity and will then observe them attempting the activity, noting the aspects they are unable to complete. If the desired activity is a significant distance from their current ability the therapist will work with the patient to establish interim steps that will act as a bridge between their current ability and their goal. The evaluation of the observed activity will allow the therapist to select appropriate exercises and level of difficulty. Exercises will be selected from a standard menu (see Additional file 1: Appendix 1 for the lower limb menu) and modified by mutual agreement between participant and therapist, to pursue and attain the desired activity. This will result in an individualised programme based on the assessment of the participant’s goals and ability. One sheet for each selected exercise, giving clear detail of parameters and a diagram of the exercise, will be left with the participant in a manual (see Additional file 2: Appendix 2 for an example of one exercise).

### Follow-up visits

The physiotherapist will check that prescribed exercises are being performed effectively and safely. If the participant is able to perform the prescribed exercises with ease, some parameters will be changed to maintain the challenge of the exercise. If the selected goal has been reached the participant will be encouraged to consider another desired activity.

Information will also be collected about exercise completion and facilitators and barriers to exercise. This will help personalise subsequent communication by phone and text messaging. The participant will be encouraged incrementally to take control over deciding on a desired activity and selecting exercises that help them reach that activity, to reduce reliance on the physiotherapist over the 6-month treatment phase.

### Telephone calls

A structured telephone interview will be used to check on progress, satisfaction with the programme and the occurrence of any barriers to completion of the exercises. Information from each interview will be used to help formulate a strategy to maximise participation in the programme. For example, if a participant reports that they are unable to complete the exercises because they do not understand the instructions, the physiotherapist will clarify or change the exercise instructions or parameters. If a participant reports that they are finding the programme too easy, the physiotherapist can provide modifications to increase the difficulty level. No new exercises will be prescribed over the phone.

### Text messages

Encouragement to continue with the exercise programme will be provided by the physiotherapist. This encouragement will be via brief text messages acknowledging progress so far and focussing on goal attainment. Participants will be encouraged to use mobile phones provided if possible, but if that is not possible, e-mail messages will be sent as an alternative. Modifications of the exercises already prescribed will be suggested via text message but no new exercises will be given. Simple checks on progress will be undertaken (with those able to use text messaging to reply).

### Telecommunication technology

Mobile phone ownership and acceptability of use has been investigated in New Zealand through focus groups undertaken by the authors in groups of community dwelling people with stroke. Preliminary results showed approximately 60% of people owned and used a mobile phone, with others having access to one if needed. However, it is acknowledged that some people will not have access to a mobile phone, so in order to increase the opportunity to participate in this trial, we will provide a mobile phone to all those undertaking ACTIV, who do not own a phone. Participants who do not own a phone will be instructed on the use of a mobile phone and then encouraged to use it to access the text messages sent as part of ACTIV. We trialled a variety of low-cost phones and selected the most straightforward devices with large keys and easy-to-read screens. Plain English instructions will be left with all ACTIV participants to improve their ability to use the mobile. A small credit will be put on all ACTIV participants’ phones, to ensure that cost of messaging is not a barrier to continuation of the programme.

### Additional support

If the participant requests information about stroke-related issues beyond the exercise programme, the physiotherapist will have information sheets commonly in use, which will be provided by the Stroke Foundation (a not-for-profit organisation supporting and representing people with stroke in the community) and will be kept in the folder used by the physiotherapist for assessment forms and other paperwork. These can be provided as required. The participant can contact the physiotherapist at any stage if an adverse event occurs, if there is confusion about the programme and instruction, or if they are unable to perform the exercises.

### Contingency planning

In the event of a concern about the participant’s health or wellbeing, the physiotherapist may gain consent from the participant to contact their emergency contact person. As a registered health care professional, the physiotherapist will access appropriate medical assistance, as they would in any other clinical setting.

### Discharge visit

The physiotherapist will check on goal achievement. If the goal has been reached the participant will be encouraged to consider the next thing they would like to achieve. If the original goal has not yet been reached the physiotherapist will encourage the participant to note the steps that have been achieved and plan the next steps needed. Encouragement will be given to continue with the exercise programme independently, focussing on exercises in ACTIV that have been useful.

### Usual-care control group

Some people with stroke re-access services following discharge from formal therapy; no effort will be made to prevent the control group receiving additional care either publicly or privately. However, participation in physical activity will be ascertained during a monthly phone call by a research assistant, independent of the study and blinded to group allocation. Participants in the control group will undergo the three assessments from the blinded assessor at baseline, 6 and 12 months.

### Data monitoring

A Data Monitoring Committee (DMC) will monitor the progress of the study. The DMC consists of the study statistician, and two researchers independent of the study. The Health Research Council of New Zealand, as the funder of this research, reviewed the proposal at its Data Monitoring Core Committee and agreed that as a low-risk study, a wholly independent DMC was not required and the partial unblinding of the study statistician was acceptable.

### Outcome measures

#### Baseline data

Baseline demographic data will be collected from all participants at the initial assessment by the blinded assessor. All quantitative outcome measures will be collected at baseline, immediately after the intervention (approximately six months after baseline assessment) and 6 months after the intervention has finished (approximately 12 months after baseline assessment).

### Primary outcome

The primary outcome measure is the physical function subcomponent of the SIS 3.0. [40]. The SIS 3.0 consists of 59 questions divided into eight domains; strength, hand function, mobility, activities of daily living, emotion, memory, communication and social participation. The four physical domains (strength, hand function, mobility and activities of daily living) can be summed to generate the physical subcomponent score. This is reported as a normalised summary score, has excellent test-retest reliability with interclass correlation (ICC) of 0.98, and the SIS has been shown to be responsive to change in this population [41]. Rasch analysis of the SIS indicates that the items are uni-dimensional with an excellent range of item difficulty [40].

### Secondary outcomes

#### Physical performance measures

Two simple physical performance measures will be used as follows: (1) a Jaymar® hand-held dynamometer (Sammons Preston, Rolyan, Bolingbrook, IL, USA) will be used to ascertain grip strength. The reliability coefficient for grip strength in the paretic arm of people with stroke is > 0.80 [42]; (2) the step test will be used to assess dynamic balance. This has been shown to have good test-retest reliability in stroke with an ICC of 0.88 [43] and has been used in RCTs of stroke-related interventions [44,45].

#### Self-efficacy

The Stroke Self-Efficacy Questionnaire (SSEQ) [46] will be used to collect data relating to the stroke participant’s confidence in their ability to undertake daily tasks that may have been difficult since their stroke. The SSEQ has been shown to have good face validity and feasibility when used in the recovery period following stroke. Its criterion validity was 0.80, when compared with the Falls Efficacy Scale [46]. Self-efficacy has been shown to be an important predictive factor in ongoing physical activity post-stroke [4].

#### Health outcomes and the impact of stroke

The SIS measures changes in both body structure and activity, and will be used to ascertain changes in health outcomes and the impact the stroke has had in various areas of the participants life; all eight domains and the overall stroke recovery rating will be used [36]. Test-retest reliability is excellent (ICC > 0.90) for all but the emotion domain, which has an ICC of 0.68 [47].

#### Hospital and residential care admission rates

Acute or emergency admission to hospital and respite or permanent admission to residential care will be collected from electronic records and stroke participant/carer responses. However only those that are a result of the stroke will be used in the economic evaluation of the intervention.

#### Economic evaluation

This study incorporates an economic evaluation alongside the study. It takes the perspective of the health funder and compares ACTIV with usual care. Direct healthcare cost associated with stroke survivorship will be assessed for all participants. One-year direct cost of stroke will be estimated using hospital electronic records and stroke participants’/carers’ survey responses. Costs will be reported for one year post-stroke and modelled over the lifetime post-stroke. For cost-effectiveness of the intervention, the cost of health services usage obtained from electronic records and the survey responses will be compared between the two groups. Responses to the EuroQol (EQ)-5D questionnaire and willingness to pay for the services will be compared to ascertain the cost utility and cost benefit of the intervention. Although no differences in mortality are expected, differences in utility will be modelled over the expected life span for stroke survivors in the community to identify the long-term cost-effectiveness of the intervention. Probabilistic sensitivity analyses will be performed to assess the robustness of the results to changes in key parameters [48]. A discrete choice experiment will be used to ascertain patient preferences for rehabilitation [49,50].

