
## Methods/design

### Study aims

The overarching aim of this study is to investigate ACTIV for people with stroke to improve the transition from hospital to community living. The specific aims are to:

1. Determine the effect of ACTIV on physical function

Primary research question: At the end of the 6-month intervention, will ACTIV improve physical function in people with stroke compared to a usual care control group, as measured by the physical subcomponent of the Stroke Impact Scale (SIS 3.0)?

Secondary research question 1: At the 12-month follow-up, will any physical gains achieved by the intervention group at the end of the intervention be maintained as measured by the physical subcomponent of the SIS 3.0?

Secondary research question 2: At the end of the 6-month intervention and at follow-up, will ACTIV improve physical function in people with stroke, compared to a usual care control group as measured by the physical performance measures and the stroke self-efficacy questionnaire?

2. Determine the effect of ACTIV on health outcomes and quality of life.

Secondary research question 3: Over the study period, will ACTIV improve health outcomes and quality of life in people with stroke compared to a usual care control group as measured by the SIS 3.0?

3. Determine the effect of ACTIV on hospital and residential care admission rates.

Secondary research question 4: Over the study period, will participation in ACTIV result in a reduction in hospital admissions compared to the usual care control group?

4. Determine the cost and cost-effectiveness of ACTIV.

Secondary research question 5: Over the study period, will ACTIV be cost-effective compared to usual care in reducing aspects of the burden of care in people with stroke?

5. Explore participant experience of and satisfaction with ACTIV.

Qualitative question: What are the experiences, in particular, the perceived benefits and challenges for participants in ACTIV?

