### Study design

This is a multi-site, two-arm, assessor blinded, parallel randomised controlled trial (RCT). Alongside the RCT, an economic evaluation will compare the cost-effectiveness of the intervention with usual care and preferences for stroke rehabilitation delivery, in addition, a qualitative component will explore the experiences of participants with the intervention. Enrolment will occur in New Zealand in the North Island at Middlemore Hospital (South Auckland), North Shore Hospital (North Auckland), and in the South Island at The Princess Margaret Hospital (Christchurch), and Dunedin Hospital (Dunedin). People will be eligible for inclusion in the study at the time of discharge from standard physiotherapy. Standard physiotherapy will include inpatient rehabilitation in general medical or specialist stroke care facilities, and outpatient or community physiotherapy post-discharge from hospital. Outcome assessments will be conducted at baseline, immediately after the six-month intervention and at six months post-intervention by an assessor blinded to group allocation. Figure 1 outlines the study design and procedure.

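### The economic evaluation counts only admissions caused by the stroke, and the one dated cost horizon in its section starts at the stroke rather than at randomisation

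*Protocol article*

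**What the plan says.** All references are to the protocol article.

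**Admissions.** The section on hospital and residential care admission rates collects acute and emergency hospital admissions, and respite or permanent residential care, from electronic records and from participants or carers. It then restricts their use: "However only those that are a result of the stroke will be used in the economic evaluation of the intervention". On perspective, the Economic evaluation section says: "It takes the perspective of the health funder and compares ACTIV with usual care". The Economic analysis section obtains net cost by comparing intervention with control patients.

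**Time window.** The Economic evaluation section states: "One-year direct cost of stroke will be estimated using hospital electronic records and stroke participants’/carers’ survey responses". It continues: "Costs will be reported for one year post-stroke and modelled over the lifetime post-stroke". The between-arm comparison comes in the next sentence, which gives no dates: "the cost of health services usage obtained from electronic records and the survey responses will be compared between the two groups". Secondary research question 5 (Study aims) asks: "Over the study period, will ACTIV be cost-effective compared to usual care in reducing aspects of the burden of care in people with stroke".

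**Entry and follow-up.** Under Study design, "People will be eligible for inclusion in the study at the time of discharge from standard physiotherapy". Randomisation follows the baseline assessment (Randomisation). The last assessment is "6 months after the intervention has finished (approximately 12 months after baseline assessment" (Baseline data).

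**The concern.** A health funder pays for an admission whatever its cause. ACTIV is a home exercise programme with a component on staying upright, so it could plausibly cause some falls or injuries and prevent others. If such an admission is judged not to result from the stroke, its cost disappears from the comparison, while any effect on EQ-5D stays in. Costs and effects would then describe different events. The judgement of cause also becomes part of the cost measurement.

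The window raises a related problem. The arms exist only from randomisation, so only costs after that point can differ because of ACTIV. A year counted from the stroke begins before randomisation and ends before the 12-month assessment. Used for the increment, it would put costs and effects on different periods, by an amount that varies between participants.

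Cost-effectiveness is a named aim, and the Background makes evidence of it a condition for adoption by health services. The primary outcome is not affected.

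**Working it through.** The plan gives no cost figure to reproduce. The check compares its rules with each other, with arithmetic on the window.

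**1. The admission rule**

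| Admission | In the health funder's cost? | Counted under the rule? | Effect on the increment |
|---|---|---|---|
| Result of the stroke | yes | yes | none |
| Other cause, unrelated to ACTIV | yes | no | none expected; removes noise |
| Other cause, brought about by ACTIV | yes | no | a cost of ACTIV is missed |
| Other cause, prevented by ACTIV | yes | no | a saving from ACTIV is missed |

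Let A be the mean cost per ACTIV participant of non-stroke admissions that ACTIV brings about, and P the mean cost of those it prevents. The all-cause increment contains A − P from these rows and the rule sets this to zero. The error (counted minus true) is 0 − (A − P) = P − A. The rule flatters ACTIV if A > P and penalises it if P > A. The documents give neither value, so the sign is unknown.

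Scale: the planned total of 96 (Sample size) gives 96/2 = 48 per arm with equal arms. One excluded admission moves an arm's mean cost by 1/48, about 2.1% of the cost of that admission. The article gives no unit cost, so this cannot be turned into money.

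**2. The cost window**

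Inputs:
- Horizon: 12 months from stroke (Economic evaluation).
- Follow-up: about 12 months from baseline, the first six being the intervention (Baseline data). Randomisation follows baseline and is treated here as simultaneous with it.
- L, months from stroke to randomisation: **not stated; assumed**. It exceeds zero for everyone, because discharge, a mailed invitation, telephone screening and a baseline visit come first (Recruitment; Randomisation). It may be short, since people discharged directly from acute wards can enter. The only hint at a typical value is the Background's remark that many patients get no physiotherapy after three months.

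Formulas, for L up to 6:
- Months of the horizon before randomisation = L
- Follow-up months covered = 12 − L
- Share of follow-up lost = L/12
- Post-intervention months covered = 6 − L

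| L (assumed) | Before randomisation | Follow-up covered | Share lost | Post-intervention months covered |
|---|---|---|---|---|
| 0.5 | 0.5 | 11.5 | 0.5/12 = 4% | 5.5 of 6 |
| 1 | 1 | 11 | 1/12 = 8% | 5 of 6 |
| 3 | 3 | 9 | 3/12 = 25% | 3 of 6 |
| 6 | 6 | 6 | 6/12 = 50% | 0 of 6 |

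The two windows coincide only at L = 0. At L = 6 the horizon would hold all six months of ACTIV delivery and none of the later period in which savings could be observed.

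**3. Noise or bias**

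Costs before randomisation have the same expectation in both arms. Including them would raise both totals and add variability to the difference without biasing it. Losing the last L months is different: whatever cost difference arises then is not observed. Costing from randomisation to 12 months gives zero pre-randomisation months and full coverage for any L.

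**The case against.** **On the window.** The Economic evaluation section can be read as two steps: a cost-of-illness estimate for stroke, to which the one-year horizon belongs, and then a separate comparison of the arms. The comparison sentence carries no post-stroke window, and research question 5 refers to the study period. A condensed article may also leave exact costing dates to a fuller plan. This stands to a large extent. A reader might infer that the incremental cost does include care before randomisation and does miss late follow-up; the article does not say so. Nor does it say that randomisation occurs months after stroke. What remains is that the section's only dated horizon, for costs and for the lifetime model alike, starts at the stroke and sits directly before the comparison. It does not fit the follow-up or research question 5.

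The lifetime model could be said to recover late costs. It extends the horizon, but modelled costs do not replace observed ones.

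**On admissions.** Disease-related costing is a recognised way to limit noise in a trial of 96, and it fits the section's stated interest in the costs of living after stroke. All admissions are still collected, research question 4 compares hospital admissions between arms, and adverse events are reported for both, so harms are not hidden. That is fair, but it does not put those admissions into the net cost, and the rule is stated outright rather than left to another document.

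A reader might also infer that the rule favours ACTIV by hiding its harms. The documents do not support this. The same rule drops non-stroke admissions that ACTIV might prevent, and the Background models its delivery on a falls-prevention programme. A fall in someone with residual impairment might also be classed as a result of the stroke.

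**Conclusion.** The point holds in two parts of unequal strength.

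**Admissions: firm.** The restriction is explicit. Followed as written, it leaves out admissions caused or prevented by ACTIV that are not judged due to the stroke, and it makes each participant's cost depend on a causal judgement. That does not fit a health-funder perspective or a between-arm net cost. The direction of bias is unknown, and its size depends on event numbers and unit costs that the article does not give.

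**Window: an inconsistency to resolve.** The stroke-anchored horizon does not match follow-up from randomisation or the study period of research question 5. Only if it were used for the between-arm comparison would the last L months of follow-up be lost: 8%, 25% or 50% at assumed delays of 1, 3 or 6 months. L months of earlier cost would then add noise, not bias.

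Both parts concern the secondary economic evaluation and should be settled before the costs are analysed.

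**What to change.** 1. State that incremental cost covers randomisation to 12 months after randomisation for every participant, the same window as EQ-5D, and start the lifetime model at randomisation.
2. Keep the one-year post-stroke cost as a descriptive cost-of-illness figure, separate from the comparison of arms.
3. Include all acute, emergency and residential-care admissions in the incremental cost. Report the stroke-related subset alongside, classified by someone blind to arm.

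The cost is small: some wording, re-dating of records, and a blinded classification of admissions that are already to be collected. The drawback is that all-cause costs will be somewhat noisier in a trial of this size, which is why the stroke-related result is worth reporting next to them.
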